### Procedures

2.4

Participants will be recruited from the Houston community through multimedia platforms (university listservs, flyers, etc.). Interested participants will complete an online screener via Qualtrics, an online data collection platform. Participants who qualify will be contacted by trained study staff who will describe the study and schedule the baseline visit. Upon arrival to the lab, participants will provide informed consent and be assessed regarding trauma history, PTSD symptomatology, substance use, and the presence of current/past bipolar or psychotic disorder, as determined by the MINI-International Neuropsychiatric Interview. A urine drug screen will be implemented at baseline to identify current substance use (not used for exclusion).

Once eligibility is confirmed, participants will be randomly assigned (equally; 50 participants per condition, using a simple randomization design) to AP-PFI or C-PFI and complete the intervention/comparison condition on laboratory computers. Participants will then complete a post-intervention assessment. Online follow-up assessment will include similar surveys and will be scheduled 1-week and 1-month after completing the intervention conditions. Participants will be compensated $25 for completing the in-person baseline assessment and $35 and $40 for completing the 1-week and 1-month follow-up surveys, respectively, for a total of $100 in eGift cards. All study procedures were approved by the University Institutional Review Board and all study measures and assessment procedures are outlined in Table 1 and Fig. 1.

**Table 1 tbl1:** Study measures and timepoints.

Measures	Items	Assessment Timepoint				
		**Screen**	**Baseline**	**Post**	**1-Week**	**1-Month**
Demographics Questionnaire	**20**	**X**				
Urinalysis drug screening	**N/A**		**X**			
Breath analysis	**N/A**		**X**			
MINI-International Neuropsychiatric Interview	**Variable**		**X**			
Treatment Credibility/Expectancy Questionnaire	**6**			**X**		
Modified Satisfaction with Treatment	**7**			**X**		
Alcohol Ladder	**1**		**X**	**X**	**X**	**X**
Modified Alcohol Use Disorders Identification Test	**3**–**10**	**X**	**X**		**X**	**X**
The Short Inventory of Problems	**15**		**X**		**X**	**X**
Alcohol Urges Questionnaire	**8**		**X**	**X**	**X**	**X**
Timeline Follow-Back	**30**		**X**		**X**	**X**
Life Events Checklist for *DSM-5*	**17**	**X**	**X**		**X**	**X**
Modified PTSD Checklist for *DSM-5*	**20**	**X**	**X**		**X**	**X**
Anxiety Sensitivity Index-3	**18**	**X**				
The Short Scale Anxiety Sensitivity Index	**5**		**X**		**X**	**X**
The Beck Suicide Scale	**21**	**X**	**X**		**X**	**X**

*Note.* MINI-International Neuropsychiatric Interview (MINI) [49]; Treatment Credibility/Expectancy Questionnaire (TCEQ) [58]; Modified Satisfaction with Treatment (SAT) [59]; Alcohol Ladder [53]; Alcohol Use Disorders Identification Test (AUDIT) [1], modified timeframe to correspond with each follow-up timepoint; The Short Inventory of Problems (SIP) [54]; Alcohol Urges Questionnaire – Short Form- Revised (AUQ) [55]; Timeline Follow-Back (TLFB) [52]; Life Events Checklist for DSM-5 (LEC-5) [50]; PTSD Checklist for DSM-5 (PCL-5) [46], modified timeframe to correspond with each follow-up timepoint; Anxiety Sensitivity Index-3 [56]; Short-Scale Anxiety Sensitivity Index (SSASI) [47]; Beck Suicide Scale (BSS) [57].

**Fig. 1 fig1:**
[figure not shown]
Study CONSORT flow diagram. Potential participants are screened to determine preliminary study eligibility. Eligible participants are invited for an in-person visit that includes (1) a baseline diagnostic and symptom assessment, (2) a brief intervention (randomized to one of two conditions: intervention or active comparison condition), and (3) a post-intervention assessment. Participants are then emailed follow-up surveys after 1-week and 1-month post-intervention.

### Intervention and comparison conditions

2.5

*Personalized feedback intervention condition (AP-PFI)*. Participants will receive a brief, 20-min computer-based AP-PFI. Both PFI will be time-matched and designed to facilitate engagement (e.g., dynamic/clickable content). Personalized content will be collected and dynamically imputed via Qualtrics and the total amount of time spent in either condition will be recorded. The content and process of the PFI will be grounded in established concepts such as the theory of planned behavior [48] and principles of motivational interviewing [13]. Specifically, AP-PFI will incorporate personalized profiles for PTSD (e.g., intensity, interference, goals for functioning); AS (e.g., beliefs about anxiety), and alcohol consumption and problems (e.g., drinking quantity/frequency, alcohol-related problems). PFI components will include normative feedback (e.g., age- and sex-specific drinking, contrasted with self-reported perceived norms); AS and PTSD feedback; and PTSD-alcohol feedback (e.g., feedback regarding positive expectations for alcohol anxiolysis). Sex- and age-specific normative data will be extracted from the extant literature. Strategies to manage and reduce drinking and AS and improve stress management are reviewed. See Table 2 for AP-PFI content.

**Table 2 tbl2:** Integrated, single-session PFI (AP-PFI) content summary.

Introduction
• **→**Introduction to AP-PFI program and use of personalized information. • **→**Participants provide a goal related to their drinking and/or mental health (e.g., *“I want to reduce my drinking because it affects my marriage”; “I want to improve my mental health because I want to be more present with my family”; “I want to drink two fewer beers on the nights I drink”*).
**Section 1:****Integrated Alcohol Feedback and Psychoeducation**
Personalized feedback on drinking patterns
• **→**Feedback based on self-reported (1) drinking pattern and (2) prediction of drinking patterns for the average person with PTSD symptoms. • **→**Corrective information is provided on how their prediction compares to actual drinking patters among adults with PTSD symptoms.
Personalized feedback on alcohol intoxication and metabolism
• **→**Feedback based on participant's estimated daily and weekly blood alcohol concentration (BAC) during and after drinking sessions based on self-reported drinking pattern. • **→**Feedback on their estimated metabolization of alcohol over time based on their height, weight, and biological sex.
Personalized feedback on alcohol-related expectances
• **→**Feedback based on self-reported positive and negative alcohol-related expectances (e.g., *“I am more accepted socially”; “I become clumsy or uncoordinated”*).
**Section 2:****Integrated PTSD Feedback and Psychoeducation on Self-Medication**
Psychoeducation on alcohol use and PTSD
• **→**Information on trauma and PTSD symptoms and their associations with increased alcohol use and problematic drinking. • **→**Defining drinking-related coping and the role and consequences of self-medication.
Personalized feedback on PTSD symptoms
• **→**Feedback based on self-reported PTSD symptoms. • **→**Normative comparisons are provided based on community adults with PTSD symptoms who do not drink versus those who drink to highlight interactions between drinking and PTSD.
Personalized feedback on PTSD-related expectances for alcohol use
• **→**Feedback based on self-reported positive consequences of drinking on PTSD symptomatology (e.g., *“My bad dreams would decrease after a few drinks”; “After a few drinks, I would be less angry or on edge”*).
Psychoeducation on self-medication
• **→**Information on the self-medication cycle between trauma, PTSD symptoms, and drinking.
**Section 3:****Integrated Anxiety Sensitivity Feedback and Psychoeducation**
Psychoeducation on anxiety sensitivity
• **→**Information on the physical, cognitive, and social dimensions of anxiety sensitivity.
Personalized feedback on anxiety sensitivity and psychoeducation
• **→**Feedback based on self-reported anxiety sensitivity symptoms. • **→**Normative comparisons are provided based on community adults who drink and report PTSD symptoms. • **→**Psychoeducation provided on associations between anxiety, PTSD, and drinking.
**Section 4: Strategies to Reduce Drinking and Improve Mental Health**
Strategies to manage and reduce drinking
• **→**Review and positive reinforcement of self-reported protective behavioral strategies already in use. • **→**Information on additional strategies that can be used to manage and reduce drinking (e.g., “*alternate alcoholic and nonalcoholic drinks”; “avoid drinking shots of liquor”*). • **→**Interactive ranking of which strategies the participant would be willing to try and likelihood of using it.
Strategies to manage stress and improve coping
• **→**Introduction and review of two breathing exercises focused on reducing and managing stress. • **→***In vivo* practice of these breathing exercises via online video instruction.
Strategies to reduce anxiety sensitivity
• **→**Introduction and review of interoceptive exposure exercises developed to decreased anxiety sensitivity. • **→**Participants are provided with detailed instructions for the following exercises: (1) narrow straw breathing, (2) over-breathing, and (3) head between legs/head-rush exercise. • **→**Interactive ranking of which exercises the participant would be willing to try and likelihood of using it.
**Section 5: Review**
• **→**Intervention content is briefly summarized and reviewed. • **→**A handout that includes all intervention content is provided to the participant at the end of the study visit.

*Comparison condition (C-PFI).* Participants in the time-matched comparison condition will receive personalized feedback on alcohol use but will not receive PTSD or AS-related personalized feedback. C-PFI will include alcohol-focused components identical to those provided in AP-PFI (e.g., alcohol profiles, normative feedback, strategies to manage and reduce drinking). Therefore, it will be possible to isolate the impact of personalized PTSD and AS feedback versus personalized alcohol feedback.

### Study measures

2.6

#### Demographics

2.6.1

*Demographic questionnaire*. Participants will be asked to self-report demographic information including sociodemographic factors, health and medical information, educational levels, and family history. The questionnaire will be used to describe the current sample and will be administered at the screening assessment timepoint.

#### Diagnostic measure

2.6.2

*MINI-International Neuropsychiatric Interview* (MINI) [49]. The MINI is a brief, structured, clinician-administered diagnostic interview to thoroughly assess common *DSM-5* disorders using *DSM-5* diagnostic guidelines. Trained doctoral students will conduct diagnostic assessments and will be supervised regarding the accuracy of their diagnosis by the principal investigator and doctoral-level raters. The MINI will be administered at baseline and will be used to assess if any exclusionary criteria are met and will serve to document psychopathology within the sample.

#### PTSD-related measures

2.6.3

*Life Events Checklist for DSM-5* (LEC-5) [50]. The LEC-5 is a 17-item, self-report questionnaire that is used to screen for 16 potentially traumatic events (e.g., natural disaster, combat, sexual assault, transportation accident) experienced at any time throughout the lifespan, including an additional item for “other” potentially traumatic events not listed. Respondents will be asked to indicate (via check mark) whether each listed event “happened to me,” “witnessed it,” “learned about it,” “part of my job,” or “not sure.” If participants endorse “happened to me,” “witnessed it,” or “part of my job” for a given item, this will be coded as positive exposure to the particular traumatic event type. Total number of exposure event types will be summed to produce a variable indicating overall trauma load. The LEC-5 will be administered during the screening assessment and will be modified for all follow-up timepoints to assess any recent trauma exposure since the previously completed timepoint.

*PTSD Checklist for DSM-5* (PCL-5) [46]. Respondents will be asked to complete the PCL-5 regarding the “worst” traumatic event endorsed on the LEC-5. The PCL-5 is a 20-item, self-report questionnaire that measures PTSD symptom severity. Each items reflects a symptom of PTSD as defined in the *DSM-5* [51]. Both past-month and past-week versions will be utilized to capture symptom change at baseline and follow-up timepoints, respectively. Respondents will be asked to rate each item on a 5-point Likert scale (0 = *Not at all* to 4 = *Extremely*) in regard to the frequency in which they have been bothered by the symptom in the past week or past month. Total summed symptom severity scores range from 0 to 80, with higher scores indicating higher symptom severity. Eligible participants will be required to endorse ≥2 symptoms (with ratings of 2 [“moderately”] or higher) in each *DSM-5* PTSD symptom cluster, which aligns with current guidelines [46]. The PCL-5 will be administered at all study timepoints.

#### Alcohol-related measures

2.6.4

*Alcohol Use Disorders Identification Test* (AUDIT) [1]. The AUDIT is a 10-item, self-report, Likert-style screening instrument developed to assess alcohol-related problems and drinking patterns. Items on the AUDIT are summed to create a total score, with higher scores indicating increased alcohol use severity. Participants will be screened with the full AUDIT to assess past-year alcohol use and the first three items of the AUDIT [i.e., AUDIT-C; 45] will be administered at all other timepoints (except the post-intervention assessment) to evaluate hazardous drinking over time. Scores will be used to assess changes in drinking and examine changes from hazardous to non-hazardous drinking. The timeframe will be modified for each timepoint to assess hazardous drinking since the previous timepoint.

*Timeline Follow-Back* (TLFB) [52]. The TLFB is a calendar-based, self-report questionnaire that collects information on the pattern, variability, and magnitude of drinking among individuals over a specific timeframe. For the current study, participants will be asked to estimate their daily consumption within the past two weeks (anchored two weeks prior to the date of their baseline assessment). The timeframe will be modified for the 1-week and 1-month follow-up timepoints to assess daily drinking between timepoints.

*Alcohol Ladder* [53]. The Alcohol Ladder is a one-item, self-report, and reliable measure that assesses an individual's motivation to change their alcohol use. It contains 10 statements, listed in ranked order, that correspond to the following stages of change: pre-contemplation, contemplation, preparation, action, and maintenance. Higher scores on the Alcohol Ladder indicate greater motivation to change one's alcohol use. Participants will be instructed to select the statement that best corresponds to their current stage. The Alcohol Ladder will be administered at baseline and at each follow-up timepoint.

*The Short Inventory of Problems* (SIP) [54] is a 6-item, self-report measure of potential consequences of drinking that is derived from the 45-item Drinker Inventory of Consequences [54]. Respondents will be asked to rate each item on a 4-point Likert scale (0 = *Never* to 3 = *Daily or almost daily*) in regard how much alcohol has led to consequences across five domains: physical, social responsibility, intrapersonal, impulse control, and interpersonal. Items are summed to produce a total score, with higher scores on the SIP indicating greater alcohol-related consequences. The SIP will be administered at baseline and 1-week and 1-month follow-up assessment timepoints (modified timeframes).

*Alcohol Urges Questionnaire–Short Form-Revised* (AUQ) [55]. The AUQ is an 8-item, self-report questionnaire that measures cravings to consume alcohol. Items on the AUQ are scored using a 7-point Likert scale (1 = *Strong disagree* to 7 = *Strong agree*) regarding current alcohol-related cravings (e.g., “All I want to do now is have a drink”). Total scores are averaged, and higher scores represent greater severity of cravings. The AUQ will be used to examine participants’ levels of alcohol-related cravings at baseline and each follow-up timepoint.

#### Affective measures

2.6.5

*Short-Scale Anxiety Sensitivity Index* (SSASI) [47]. The SSAI is a 5-item self-report measure that assesses anxiety-related interoceptive sensations and cognitions. The SSASI was derived from the original 18-item *Anxiety Sensitivity Index-3 (ASI-3)* [56]. Each item is rated using a 4-point Likert scale (0 = *Very little* to 4 = *Very much*) in regard to how much a respondent agrees with the specific statement being rated, with higher scores indicating greater severity of AS. For the current study, the total score of the SSASI (i.e., the sum of all 5 items) will be used to indicate the severity of an individual's AS and will be administered at each timepoint (except the post-intervention assessment) and the total score of the ASI-3 will be used to assess study inclusion criteria (elevated AS score [≥17]) during the screening timepoint.

*Beck Suicide Scale* (BSS) [57]. The BSS is a 21-tem, self-report measure that assesses the severity of an individual's suicidal ideation or desire to die. Respondent's rate, on a 3-point scale, the most accurate statement for the intensity of past-week suicidal ideation (e.g., “I have no wish to live”), with higher summed total scores indicating more severe suicide ideation. The BSS will be administered at each timepoint (except the post-intervention assessment) to assess suicide risk**.**

#### Intervention-related measures

2.6.6

*Treatment Credibility/Expectancy Questionnaire* (TCEQ) [58]. The TCEQ is a 6-item, self-report, and reliable index [58] that will be used to assess perceptions of intervention credibility/expectancies, including satisfaction and acceptability of AP-PFI relative to C-PFI. The TCEQ will also be employed to assess how participants think the intervention will be successful in terms of reducing alcohol use, PTSD symptoms, and AS, while also assessing anticipated reductions in drinking, PTSD symptoms, and AS (0–100%). Items on the TCEQ are rated on Likert-style scales from 1 (*not at all*) to 9 (*very*), with higher summed scores indicating greater positive perceptions of the intervention received by the participant. The TCEQ will be administered in the post-intervention assessment.

*Satisfaction with Treatment* (SAT) [59]. The SAT is a 7-item, self-report measure that will be used to measure participants’ positive and negative experiences with the computerized format of the intervention. A modified version of the SAT will be used for the current study. Participants will be asked to report the degree of satisfaction with the PFI interventions (e.g., AP-PFI or C-PFI) using a Likert-style rating scale and qualitative-based questions. Likert-style rated items will be summed to produce a total satisfaction score, with higher scores indicating greater satisfaction with the intervention received by the participant. The SAT will be administered in the post-intervention assessment.

### Data analytic plan

2.7

Data will first be examined for multivariate normality; the maximum likelihood (ML) estimator will be used if data are approximately normal, and robust maximum likelihood will be used if the data are not multivariate normal. Categorical outcomes (i.e., hazardous drinking status) will be estimated using the mean and variance adjusted weighted least squares estimator when appropriate. Missing data will be handled using direct ML techniques within MPlus [60] under a missing at random assumption [61]. Differences in key baseline characteristics between randomly assigned intervention condition groups will be assessed and significant characteristics will be used as covariates to determine the influence of any potential randomization failures on results. Latent growth models (LGM) will be used to model linear trajectories of change in outcomes. Evaluation of LGM model fit will be examined using fit diagnostics (i.e., standardized residuals) and fit statistics (i.e., root mean square error of approximation) following recommended cutoffs [62].

*Aim 1.* To evaluate the feasibility and acceptability of AP-PFI vs. C-PFI, initial metrics of feasibility and efficacy will be examined, including (1) recruitment/retention rates throughout the duration of the study, (2) intervention acceptability at post-intervention, intervention utilization at 1-week and 1-month follow-up, and (3) initial efficacy at post-intervention, 1-week, and 1-month follow-up. Retention between conditions will be assessed utilizing binary logistic regression to examine condition (0 = control; 1 = PFI) as a predictor of each follow-up completion (0 = missed; 1 = completed). Effect sizes will be calculated with Cohen's *d* for frequency and proportions [i.e., of completed follow-ups; 63]. Intervention acceptability will then be evaluated with condition as a predictor of acceptability items (i.e., TCEQ, SAT); theoretically relevant variables such age, sex, and racial/ethnic minority status will be included as covariates. Cohen's *d* for mean differences will be calculated [63].

*Aim 2*. Hypotheses for Aim 2 (i.e., efficacy and intervention effects) will be examined using regression-based approaches, effect sizes (with 95% confidence intervals [CI]), and LGM using Mplus [60,62,64]. We will first estimate between-group differences with regression-based approaches by calculating odds ratios or Cohen's *d* effect sizes (with 95% CI) for the primary post-intervention outcomes (i.e., motivation/intention to reduce drinking) and primary 1-week and 1-month follow-up outcomes (i.e., change in rates from hazardous to non-hazardous drinking, frequency and quantity of alcohol consumption and negative consequences of drinking, and PTSD symptomatology). We will then conduct a series of conditional LGMs to examine the impact of intervention condition over time on the 1-month follow-up outcomes. A dummy code representing intervention condition will be included in the model as a predictor of the slope factor to quantify the effect of the PFI on the outcomes.

*Exploratory aim 3*. Similar modeling procedures will be used to test mechanisms of change. After conducting univariate LGM to explore changes in the putative mediators (i.e., motivation/intention to reduce drinking and levels of AS) as a function of condition, we will conduct a series of parallel process LGMs to examine how changes in the mechanisms relate to changes in primary follow-up outcomes at each assessment point. The effects of changes in the mechanisms of change on the outcomes will be examined by specifying the slope factor for each potential variable as a predictor of the slope factor for each outcome. The indirect effects of condition on outcomes via the hypothesized mechanisms will be evaluated by bootstrapped CI. Further, given the purported interaction effect of sex and a family history of AUD, dummy coded variables (0 = female, 1 = male; 0 = no history, 1 = history; respectively) will be included as additional predictors of slope in the LGM parallel process models.

*Sample size and power.* Power calculations were performed to statistically determine the target sample size of *N* = 100 for this pilot study**.** Small-to-moderate effects of the AP-PFI on primary follow-up outcomes and the hypothesized mechanisms are expected, and moderate-to-large associations (*r* > .30) between changes in the mechanisms and changes in 1-month follow-up outcomes are expected. Monte Carlo simulation studies [65] with 10,000 repetitions to identify the sample sizes necessary to detect effects indicated that the targeted sample size of 100 participants would yield 80% power to detect small-to-moderate effects for primary study aims at alpha = .05. Additionally, extant guidelines for pilot RCT designs [66] indicate that a targeted sample size of 100 participants would yield 90% power to detect small-to-moderate effects for study aims set at alpha = .05. Thus, the target sample size is well above current guidelines for pilot studies in clinical research [67].

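### When weighted least squares is used for hazardous-drinking status, the direct-ML, missing-at-random handling promised in the next sentence does not apply to that primary outcome

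*Protocol article*

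**What the plan says.** Section 2.7 (Data analytic plan) of the protocol article opens with the estimators. Maximum likelihood, or its robust form, is for data that are or are not multivariate normal. For the binary outcome: "Categorical outcomes (i.e., hazardous drinking status) will be estimated using the mean and variance adjusted weighted least squares estimator when appropriate". The sentence after it reads "Missing data will be handled using direct ML techniques within MPlus", under an assumption of missing at random. It makes no exception for categorical outcomes.

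The Aim 2 paragraph of the same section lists "change in rates from hazardous to non-hazardous drinking" among the primary 1-week and 1-month outcomes. It sets two steps. The first is "regression-based approaches by calculating odds ratios" or Cohen's d with 95% confidence intervals; no estimator is named for it. The second is "We will then conduct a series of conditional LGMs to examine the impact of intervention condition over time on the 1-month follow-up outcomes". Logistic regression is named only in the Aim 1 paragraph, and there for follow-up completion: "Retention between conditions will be assessed utilizing binary logistic regression".

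**The concern.** Direct maximum likelihood under missing at random works because each participant contributes the likelihood of whatever he or she provided. Someone seen at 1 week but lost at 1 month still informs the 1-month result through the modelled link between the two.

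Mean- and variance-adjusted weighted least squares does not do this. It fits univariate and bivariate probit summaries to whoever is available at each occasion or pair of occasions, then fits the model to those summaries. There is no casewise likelihood to which direct ML could apply. The estimator stays valid if dropout depends only on arm and the covariates in the model. It is not protected if dropout depends on an earlier outcome, such as 1-week drinking, which is a case that missing at random is meant to cover.

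This outcome is exposed to that weakness. Follow-ups are online surveys (section 2.4) sent by email (Fig. 1 legend), and the plan itself tests whether completion differs by condition. Hazardous drinking is an inclusion criterion (section 2.3), so baseline status will hardly vary. One-week status is then the main earlier information on this outcome, and the estimator does not use it to correct for 1-month dropout. What is at stake is a primary comparison reported as valid under missing at random when it is not.

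**Working it through.** **No figure in the plan to reproduce.** The article gives no dropout rate, no expected rate of hazardous drinking and no correlation between occasions. All rates below are assumptions. They show when bias arises, not how large it will be in this trial.

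**Illustration 1: closed form.**

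Assumed inputs:
- Hazardous at 1 week: 70% in C-PFI, 55% in AP-PFI.
- Hazardous at 1 month: 85% of those hazardous at 1 week, 30% of the others, in both arms.

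True 1-month proportion = p₁ × 0.85 + (1 − p₁) × 0.30, where p₁ is the 1-week proportion:
- C-PFI: 0.70 × 0.85 + 0.30 × 0.30 = 0.685
- AP-PFI: 0.55 × 0.85 + 0.45 × 0.30 = 0.6025
- True difference: 0.0825, or 8.25 points

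Available-case proportion = [p₁(1 − m₁) × 0.85 + (1 − p₁)(1 − m₀) × 0.30] / [p₁(1 − m₁) + (1 − p₁)(1 − m₀)], where m₁ and m₀ are 1-month dropout among those hazardous and not hazardous at 1 week.

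*Dropout follows 1-week drinking in one arm only* (C-PFI 15% throughout; AP-PFI m₁ = 30%, m₀ = 5%):
- C-PFI: 0.685, unchanged
- AP-PFI: (0.55 × 0.70 × 0.85 + 0.45 × 0.95 × 0.30) / (0.55 × 0.70 + 0.45 × 0.95) = 0.4555 / 0.8125 = 0.561
- Difference: 12.4 points, against 8.25 true

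*Same pattern in both arms* (m₁ = 30%, m₀ = 10%):
- C-PFI: 0.4975 / 0.76 = 0.655
- AP-PFI: 0.44875 / 0.79 = 0.568
- Difference: 8.7 points, against 8.25 true

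Maximum likelihood on 1-week and 1-month status jointly weights the 1-month proportion within each 1-week group by the full 1-week distribution. It therefore returns 0.685 and 0.6025 in both patterns.

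**Illustration 2: other rates, with a simulation.** Assumed hazardous status is 0.85 at 1 week and 0.80 at 1 month in C-PFI, and 0.75 and 0.60 in AP-PFI. The true 1-month odds ratio is (0.60/0.40) / (0.80/0.20) = 0.375 and the true risk difference is −0.20. Odds ratios are large-sample values for latent correlations of 0.5 to 0.8. Risk differences are means over 20,000 simulated trials of 50 per arm at correlation 0.7.

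| 1-month dropout | Available-case OR | Available-case risk difference | Joint ML risk difference |
|---|---|---|---|
| By arm only (10% C-PFI, 20% AP-PFI) | 0.375 | −0.201 | −0.201 |
| By 1-week status, same in both arms (30% / 5%) | 0.373 to 0.375 | −0.210 | −0.200 |
| By 1-week status in AP-PFI only (40% / 5%; C-PFI 15%) | 0.295 to 0.327 | −0.250 | −0.200 |
| By 1-week status, opposite directions (C-PFI 5% / 40%; AP-PFI 40% / 5%) | 0.242 to 0.295 | −0.275 | −0.201 |

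The two illustrations agree. There is no bias when dropout depends on arm alone, little when it follows earlier drinking alike in both arms, and material bias when it follows earlier drinking differently by arm. Both concern the raw 1-month contrast. Neither computes the bias in the effect of condition on the growth slope, which is the second-step quantity in Aim 2.

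**The case against.** The strongest defence is that the estimator sentence is conditional. Its closing qualifier leaves room for a likelihood method where weighted least squares does not suit, and the direct-ML sentence may be meant for the ML and robust-ML models named just before. Estimator detail by outcome is also often left to an analysis plan. This stands in part: the plan is not bound to weighted least squares in every analysis of this outcome. But the qualifier gives no criterion, and whenever the estimator is used the missing-data sentence is wrong for that outcome. The article chose to state both methods, so this is not a detail merely left out.

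Three stronger readings are tempting, and the document does not support them.

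- *That the binary result loses all protection against missing data.* It does not. The estimator is valid when dropout depends only on arm and modelled covariates.
- *That the promised odds ratios contradict a probit estimator.* The odds ratios belong to the first-step regressions, which have no named estimator, and the article does not say that they come from weighted least squares. A logistic model there is possible. The link is unclear; it is not a contradiction.
- *That the effect will be overstated by about half* (12.4 / 8.25 = 1.51). That ratio comes from assumed rates and a dropout pattern placed in one arm only. With about 42 and 41 participants observed, the standard error of the difference is √(0.685 × 0.315 / 42.5 + 0.561 × 0.439 / 40.6) ≈ 10.6 points. The assumed bias of 4.2 points is then about 0.4 of a standard error, in a trial described as a pilot.

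The reach is also limited. The other listed primary outcomes, if analysed as continuous, fall under ML or robust ML and are untouched.

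**Conclusion.** The point holds in limited form. For hazardous-drinking status, a listed primary outcome, the article pairs an estimator with a missing-data method that the estimator cannot carry out. Where weighted least squares is used, validity requires that dropout depend on nothing beyond arm and modelled covariates, which is narrower than the stated missing-at-random assumption.

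The consequence is conditional. Material bias needs 1-month dropout to depend on 1-week drinking differently in the two arms. Its size in this trial cannot be determined, because no dropout or status rates are given. No figure in the article is shown to be wrong. The matter deserves correction before analysis because the remedy is cheap and the report would otherwise make a claim about a primary outcome that its named method does not support.

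**What to change.** State one coherent rule for hazardous-drinking status. Either of these would do:

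1. Full-information maximum likelihood with a logit link, modelling 1-week and 1-month status jointly, with condition and continuous baseline drinking (AUDIT-C, TLFB) as covariates. The joint modelling is what brings in the 1-week information; a logit link on 1-month status alone would not. Baseline hazardous status should not be relied on, because eligibility makes it nearly constant.
2. Weighted least squares after multiple imputation that uses condition, baseline drinking and 1-week drinking, with the effect reported on the probit scale.

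As a clarification, name the model that yields the first-step odds ratios in Aim 2, since weighted least squares gives probit coefficients.

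The cost is small. Option 1 is a different estimator setting in the same software with a somewhat longer run time, and RMSEA, which section 2.7 plans to use for judging fit, is not available for this outcome. Option 2 adds an imputation step. No data collection changes.
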